### 7.3 Discontinuation of Trial

The following incidents will lead to discontinuation of a patient from the trial:

#### 7.3.1 Withdrawal of Consent

Legal guardian(s) of the subjects may withdraw his/her/their consent to trial participation at any time without the need to justify the decision. If legal guardian(s) of the subject wants to withdraw his/her/their consent, the investigator should explain the difference between treatment discontinuation and withdrawal from trial participation, including the options for continued follow-up after discontinuation of the study medication (see section 7.2).

If the legal guardian(s)'s withdraw their consent for further study visits, they should be asked if they give their consent to take part at least in V12 (visit with 24 months of age) with respect to the primary endpoint measurement. The consent has to be as an additional agreement in written form on the last given written Informed Consent Form. 7.3.1

The withdrawal of consent has to be documented in the source data.

Usually, the legal guardian(s) of the subject's withdrawal of consent only relates to future information. Therefore, the sponsor may retain and continue to use any data collected before the withdrawal of consent.

#### 7.3.2 Lost to Follow-up

Subjects will be considered lost to follow-up if they fail to return for visits and their caregiver(s) cannot be contacted by the trial site. Site personnel is expected to make diligent attempts to contact caregiver(s) of the subjects who did not appear for a scheduled visit or were otherwise not accessible by the site. These contact attempts should be documented in the subject's medical record.

#### 7.3.3 Death

### 7.4 Criteria for Discontinuation of Dose Escalation

Not applicable.

|                                                                    |                                              |                                |
|--------------------------------------------------------------------|----------------------------------------------|--------------------------------|
| Clinical Trial Code: PROTECT
EU trial number: 2022-502332-39-00 | Trial Protocol
(Version 06; (01.10.2024)) | Page 82 of 110
CONFIDENTIAL |
|--------------------------------------------------------------------|----------------------------------------------|--------------------------------|

## 7.5 Temporary Halt of the Clinical Trial

A temporary halt of a clinical trial is defined as an unforeseen interruption not provided in the protocol but with the intention to resume it. A temporary halt can be part of an urgent safety measure. If the reason for the temporary halt has the potential to affect the benefit-risk balance, the re-start is only possible through a substantial modification.

## 7.6 Early Termination of the Clinical Trial

Early termination is defined as the premature end of a clinical trial before the conditions specified in the protocol are met.

The following reasons or events may result in an early termination:

- The information on the product leads to doubt as to the benefit-risk ratio and safety concerns arise, the sponsor reserves the right to interrupt or terminate the trial, also if new scientific information make continuation unnecessary or impossible.
- Subject enrolment is insufficient and that it cannot be expedited by appropriate measures so that it is no longer possible to evaluate the primary endpoint.

DSMB recommends termination of the clinical trial or of treatment arms (see also section 12.5.1). An early end of the trial due to early inclusion of the total number of subjects is not considered an early termination. In the event of premature discontinuation of the trial for any reason whatsoever, the regulatory authorities should be informed according to applicable regulatory requirements. In case of an early termination of the trial, the date of the early termination will be the date of the end of trial. All involved investigators have to be informed immediately about a cessation / suspension of the clinical trial. The decision is binding to all clinical trial centres and investigators.

When the clinical trial is closed, all clinical trial materials (e.g. unused questionnaires) must be returned to the sponsor.

## 7.7 Premature Close-out of a Site

Premature closure of a single trial site by the sponsor may be considered for the following reasons:

- The investigator failed to recruit any subjects even though he/she had received all IMPs, means and information necessary to perform the clinical trial and had reasonable time to do so.
- Non-compliance of the investigator, sub-investigator or delegated staff with ICH-GCP, any provision of the clinical trial protocol or breach of the applicable laws and regulations.
- Structural problems and / or shortage of staff at trial site which affect the safe conduct of the study.
- Premature termination of a single centre is also possible if the sponsor notices that the conduction of the clinical trial is not compliant with ICH-GCP and / or the protocol and / or the quality of the data is insufficient.

The investigator may terminate participation in the trial himself/herself if at his/her own discretion the site or the investigator becomes unable to perform or complete the clinical trial according to the agreement in place. If this is possible at the discretion of the principal investigator, study participants already enrolled will be followed up until the end of the trial, or transferred to a nearby study site.

In the event of premature close-out for any reason whatsoever, the regulatory authorities should be informed according to applicable regulatory requirements. When trial site is closed, all clinical trial materials must be returned to the sponsor.

|                                                                    |                                              |                                |
|--------------------------------------------------------------------|----------------------------------------------|--------------------------------|
| Clinical Trial Code: PROTECT
EU trial number: 2022-502332-39-00 | Trial Protocol
(Version 06; (01.10.2024)) | Page 83 of 110
CONFIDENTIAL |
|--------------------------------------------------------------------|----------------------------------------------|--------------------------------|

## 8. Adverse Events

### 8.1 Definitions

#### 8.1.1 Adverse event

According to GCP, an adverse event (AE) is defined as follows: Any unexpected medical occurrence in a subject to whom a medicinal product is administered and which does not necessarily have a causal relationship with this treatment. An AE can therefore be any unfavorable and unintended sign (including an abnormal laboratory finding), symptom, or disease temporally associated with the use of an investigational medicinal product (IMP), whether or not related to the IMP.

An AE may be:

- New symptoms/medical conditions
- New diagnosis
- Changes of laboratory parameters which are considered as clinically significant
- Occurrence of new pathological and clinically relevant findings
- Aggregation of pre-existing symptoms in physical and neurological examinations, vital signs, ECGs, clinical chemistry, haematology etc.

The criteria that should be considered when determining whether an abnormal test finding should be reported as adverse event are as follows:

1. Test result is associated with accompanying symptoms, and/or
2. Test result requires diagnostic testing or medical/surgical intervention, and/or
3. Test result leads to a change in clinical trial dosing outside the protocol-stipulated dose adjustments, or discontinuation from the clinical trial, significant additional concomitant drug treatment, or other therapy, and/or
4. Test result is considered clinically relevant at the discretion of the investigator or sponsor
5. Intercurrent diseases and accidents
6. Worsening of medical conditions/ diseases existing before clinical trial start
7. Recurrence of disease
8. Increase of frequency or intensity of episodic diseases.

A pre-existing disease or symptom will not be considered an adverse event unless there will be an unexpected change in its intensity, frequency or quality. This change will be documented by an investigator (see also above).

Surgical procedures themselves are not AEs; they are therapeutic measures for conditions that require surgery. The condition for which the surgery is required may be an AE. Planned surgical measures permitted by the clinical trial protocol and the condition(s) leading to these measures are not AEs, if the condition leading to the measure was present prior to inclusion into the clinical trial.

In the latter case the condition should be reported as medical history.

AEs are classified as "non-serious" or "serious".

|                                                                    |                                              |                                |
|--------------------------------------------------------------------|----------------------------------------------|--------------------------------|
| Clinical Trial Code: PROTECT
EU trial number: 2022-502332-39-00 | Trial Protocol
(Version 06; (01.10.2024)) | Page 84 of 110
CONFIDENTIAL |
|--------------------------------------------------------------------|----------------------------------------------|--------------------------------|

### 8.1.2 Serious Adverse Event

Serious adverse event (SAE) is any unexpected medical occurrence that at any dose:

1. Results in death
2. Is life-threatening (the term life-threatening refers to an event in which the subject was at risk of death at the time of event and not to an event which hypothetically might have caused death if it was more severe)
3. Requires inpatient hospitalization or prolongation of existing hospitalization
4. Results in persistent or significant disability/ incapacity\*
5. Is otherwise medically relevant

\* Persistent or significant disability or incapacity means that there is a substantial disruption of a person's ability to carry out normal life functions. The irreversible injury of an organ function (e.g. paresis, diabetes, cardiac arrhythmia) fulfils this criterion.

Medical and scientific judgement should be exercised in deciding whether expedited reporting to the sponsor is appropriate in other situations - such as important medical events that may not be immediately life threatening or result in death or hospitalization but may jeopardize the subject or may require intervention to prevent one of the other outcomes listed above. These should also usually be considered serious (examples of such events are intensive treatment in an emergency room or at home for allergic bronchospasm; blood dyscrasias or seizures that do not result in hospitalization).

However, since the following events do not change the ongoing benefit-risk assessment of the current clinical trial, they do not need to be reported as SAEs:

- Hospitalization aiming exclusively at diagnostic measures, SOC treatment, or due to technical, practical or social reasons, i.e. hospitalization without underlying adverse event

### 8.1.3 Serious Adverse Reaction

SAEs that potentially may be attributed to the investigational medicinal product (IMP) are to be classified as Serious Adverse Reactions (SARs).

### 8.1.4 Adverse Events of Special Interest (AESI)

The following events are defined as adverse events of special interest (AESI) in the current clinical trial and have to be reported by investigator in accordance with the requirement for reporting of SAE, even if none of the seriousness criteria apply:

- **Clinically significant elevation of AST and/or ALT** (grade 3 or grade 4) in combination with clinically significant elevation of total bilirubin will be reported as AESI (Hy's Law).
- Clinical apparent infection leading to unplanned medical consultation without hospitalization
- Unexplained rashes (e.g. petechial rash) leading to unplanned medical consultation without hospitalization

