### 1.3.8 Long-term tolerability of sirolimus in neonates and young infants

Information on the tolerability and long-term effects of sirolimus on growth, development, and maturation of relevant organ systems in this young age group is limited. Maria *et al.* presented data of a 5-year follow-up study of 22 children with hyperinsulinemic hypoglycaemia (CHI) with a median age at start of sirolimus treatment of 3.87 months and a median starting dose of 0.96 mg/m^2/d [46]. Side effects of treatment occurred in 86.4% with a median delay of 13 months (range 1-52). Infections were most commonly reported (17/22). No growth disturbances or failure to thrive were observed. A review of the off-label use of sirolimus and everolimus in 101 published reports of diverse indications, including 255 children with TSC treated with sirolimus at a median dose of 3.6 mg/m^2/d, did not report relevant long-term use complications of treatment [44]. The experience with sirolimus in kidney transplant patients shows a good overall safety profile and was associated with a lower risk of developing malignancies compared to other immunosuppressants [47]. A retrospective, multicenter chart review of severe adverse events (SAE) associated to sirolimus “off-label” therapy for vascular anomalies identified 17 SAEs in 14 patients. The age at initiation of sirolimus therapy was under 2 years (n = 5), 2–6 years (n = 5), and older than 12 years (n = 4). SAEs occurred during the first 3 months of therapy (n = 7), between 3 and 12 months (n = 7) and after 1 year of therapy (n = 3). The most frequent SAE was viral pneumonia (n = 8) resulting in one death due to a metapneumovirus infection in a 3-month-old child and a generalized adenovirus infection in a 28-month-old child. Sirolimus blood level at the time of SAEs ranged between 2.7 and 21 ng/L [32]. In a study of pediatric liver transplant recipients (n=50) under therapy with everolimus in combination with reduced tacrolimus or cyclosporine A, most male patients (87.5%) had testosterone levels below normal range. This was not associated to changes in height or weight percentiles. Among patients available for Tanner staging after 12 months of therapy, all patients aged <8 years belonged to Tanner stages 1 or 2. No events of abnormal sexual maturation were reported during the study period. Although limited by sample size, these findings indicate that combination of mTOR inhibitors such as everolimus with tacrolimus or cyclosporine A does not appear to negatively impact linear growth or sexual maturation in pediatric liver transplant recipients up to 12 months post treatment initiation [48]. Other clinical data on potential adverse effects on longitudinal growth in renal transplant recipients is inconclusive [49, 50], and information on the effects of low-dose treatments with sirolimus on organ development and growth is lacking. Given the lack of data, we additionally assessed available information from

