## 9.5 Secondary Analyses

### 9.5.1 Main Trial Analyses

**All secondary parameters** will be analyzed for the FAS.

BSID-III cognitive scale at the age of 1 year will be analysed similar to the primary endpoint. In addition, the BSID-III cognitive scale and important subscales will be analysed descriptively by group and time point using standard descriptive measures for continuous variables. The VABS total scales, important VABS subscales, ADOS total scales, and important ADOS subscales will be analysed descriptively by group and time point using standard descriptive measures for continuous variables, as well. In addition, for cognitive impairment and autism spectrum disorders at 1 and 2 years of age, 95% CIs will be calculated by treatment group in addition to the relative frequencies using the method of Wilson. The M-CHAT-R/F and TAND will be analysed descriptively by group and time point using absolute and relative frequencies.

The MRI characteristics (as defined in Section 6.8) will be analysed by group and time point, i.e. randomization (last image before randomization) and at 2 years of age  $\pm$  6 months.

Seizure characteristics, EEG characteristics, abdominal sonography characteristics, ECG and echocardiography characteristics (as defined in Section 6.8) will be analysed by treatment group and time point (if applicable).

All **safety parameters** will be analyzed for the SAF. Only treatment emergent-event adverse events will be analysed. Frequencies (number of adverse events & number and percentage of patients with at least one adverse event) will be tabulated according to system organ class and preferred term. One table each will be created showing: all adverse events, all serious adverse events, all adverse events of special interest, all non-serious adverse events, all adverse events leading to death, all adverse events related to the treatment (treated group only), all adverse events by severity. In addition, adverse events and special situations will be analysed by categories defined in the eCRF (number of events & number and percentage of patients with at least one event).

For laboratory values and vital signs, the analyses will be conducted by visit and shift tables comparing all values by visit to the relevant baseline value will be displayed additionally.

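### The infection and rash AESI definitions exclude admitted cases, so the AESI table read alone can understate or reverse a difference between arms

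*Protocol*

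**What the plan says.** Section 8.1.4 lists three AESIs. Two are limited to events that did not lead to admission: "Clinical apparent infection leading to unplanned medical consultation without hospitalization" and "Unexplained rashes (e.g. petechial rash) leading to unplanned medical consultation without hospitalization". The third, raised transaminases together with raised bilirubin, has no such limit. The lead-in gives the purpose of the category: these events "have to be reported by investigator in accordance with the requirement for reporting of SAE, even if none of the seriousness criteria apply".

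Admitted cases are serious adverse events (SAEs) under section 8.1.2, where one criterion is "Requires inpatient hospitalization or prolongation of existing hospitalization". The exemption in that section reaches only admissions for diagnostic, standard-care or social reasons, "i.e. hospitalization without underlying adverse event", so a child admitted for an infection is not exempt.

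AESI then appears twice as an analysis category. Section 2.2.1 names it with AEs and SAEs in secondary endpoint 9, to be compared between groups. Section 9.5.1 says: "One table each will be created showing: all adverse events, all serious adverse events, all adverse events of special interest". It goes on to tables of non-serious AEs and of AEs by severity. Frequencies are given by system organ class and preferred term, as numbers of events and of patients.

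**The concern.** A category built to widen expedited reporting is reused, unchanged, as an outcome. As a reporting trigger the limit does no harm, since admitted cases are already reported as SAEs. As an outcome it means that a child seen for bronchitis and sent home is counted, while a child admitted with viral pneumonia is not.

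This matters for three reasons.

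- Infection is a risk that the protocol itself stresses (section 5.5.4.1). In the chart review of sirolimus in vascular anomalies cited in section 1.3.8, which found 17 SAEs, "The most frequent SAE was viral pneumonia (n = 8) resulting in one death".
- Admission may be affected by treatment. It may also be decided by people who know the arm, because section 5.1.2 says that trial personnel and patients cannot be blinded. The same infection could be an AESI in one arm and not in the other.
- The AESI table would mix one category counted whether or not the child is admitted (the liver criterion) with two that leave admitted cases out.

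A reader who takes the AESI row as the trial's infection result could therefore be misled about the direction of a difference.

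**Working it through.** **Step 1: follow the definitions.** The protocol states no infection or AESI rate, so there is no figure to reproduce. Applying sections 8.1.2, 8.1.4 and 9.5.1 to three records gives:

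| Record | AESI table | SAE table | All-AE and severity tables |
|---|---|---|---|
| Infection, unplanned visit, sent home, no seriousness criterion met | yes | no | yes |
| Infection, admitted | no | yes | yes |
| Unexplained petechial rash, admitted | no | yes | yes |

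The second and third records would be AESIs only if they also met the liver criterion. No table described in section 9.5.1 joins the non-admitted and admitted infections that needed medical attention. The SAE table holds only serious ones. The all-AE table also includes infections for which nobody was consulted.

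**Step 2: what this can do to the arm comparison.** For each arm (C = control, T = sirolimus), let p be the share of children with at least one infection leading to consultation or admission. Let h be the share of those children whose infections all led to admission. A child with one admitted and one non-admitted infection still counts as an AESI patient, so only h is lost:

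- AESI patient rate = p × (1 − h)
- The AESI difference is zero when h_T = 1 − p_C × (1 − h_C) / p_T

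All rates below are assumptions; only the 30 children per arm (section 4.1) come from the protocol. Take p_C = 40%, p_T = 60% and h_C = 10%. The control AESI rate is 0.40 × 0.90 = 36%.

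| h_T | AESI, sirolimus | AESI, control | Difference |
|---|---|---|---|
| 10% | 0.60 × 0.90 = 54% | 36% | +18 points |
| 20% | 0.60 × 0.80 = 48% | 36% | +12 points |
| 40% | 0.60 × 0.60 = 36% | 36% | 0 |
| 50% | 0.60 × 0.50 = 30% | 36% | −6 points |

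If admitted infections were counted too, every row would read 60% versus 40% (18 versus 12 of 30).

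**Step 3: sensitivity of the break-even.** With h_C = 10%, the difference vanishes at these values of h_T:

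- 40% versus 50% infected (control versus sirolimus): 1 − 0.36/0.50 = 28%
- 50% versus 70%: 1 − 0.45/0.70 = 36%
- 40% versus 60%: 1 − 0.36/0.60 = 40%
- 30% versus 50%: 1 − 0.27/0.50 = 46%

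**Step 4: where the excess goes.** In the 40%/60% break-even case, the SAE table shows infection in at least 0.60 × 0.40 = 24% of sirolimus children and 0.40 × 0.10 = 4% of controls (about 7 versus 1 of 30). The all-AE table contains all 18 and 12 children, plus any whose infections needed no consultation. The excess leaves the AESI table but stays visible elsewhere.

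**The case against.** The strongest reply is that AESI and SAE are complementary by design. Both go on the same form within 24 hours (section 8.7.1) and both get a second assessment (section 8.8.1), so safety oversight loses nothing. Endpoint 9 names AEs, SAEs and AESIs together, the analysis is descriptive, and nothing is decided on the AESI count alone. Tabulation at system-organ-class level groups infections, and section 9.3 leaves further detail and added analyses to the statistical analysis plan. All of this stands, and it keeps the point small.

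The size is also open to challenge. Reversal needs a large gap between arms in the share of children with only admitted infections. Over 21 to 24 months of treatment many children may have several infections, and one non-admitted infection keeps a child in the AESI count. The protocol's own cited cohort of 17 young children reports recurrent infections in 7 (section 1.3.7.1). The 8 pneumonias among 17 SAEs describe the make-up of collected events in another disease and give no rate for this trial.

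The reply does not remove the mismatch. The definition is fixed in the protocol, as is its use as a named outcome with its own table. The AE fields listed in section 8.6.1 include neither consultation nor admission, so the combined group cannot be read directly from those fields.

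**Conclusion.** The point holds in a limited form. As written, infections and unexplained rashes leading to admission are outside the AESI count unless they meet another AESI definition. The AESI table read alone can therefore understate or reverse a difference if sirolimus moves infections towards admission. How far depends on rates that the protocol does not give. On the assumed rates above, a 20-point excess disappears when 40% of infected sirolimus children, against 10% of infected controls, have only admitted infections.

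A reader might infer three stronger things that the protocol does not support:

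- **That severe infections are dropped.** The limit is on admission, not on grade. Section 8.4.1 separates seriousness from severity, and a high-grade infection seen unplanned and managed without admission remains an AESI.
- **That a sirolimus excess would be hidden in the trial.** Admitted infections appear by arm in the SAE, all-AE and severity tables.
- **That secondary endpoint 9 as a whole is biased towards sirolimus.** Its SAE component contains the missing cases; only the AESI component is affected.

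This is a minor improvement worth making because it costs almost nothing.

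**What to change.** Keep the reporting rule in section 8.1.4. For the AESI part of endpoint 9 and for the AESI table, define infections and unexplained rashes of special interest as those leading to an unplanned consultation or to admission. Tabulate them together by arm, with a split by admitted yes/no. Section 9.3 allows changes outside the primary analysis to be recorded in the statistical analysis plan only. Alternatively, reword the two definitions in section 8.1.4 to cover consultation or admission.

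The cost is one definition change and one admission flag on the AE record. No additional reports arise, because admitted cases already go on the same SAE/AESI form within the same 24 hours.
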